## Abstract

**Background:**

Exergames have the potential to provide an accessible, remote approach for poststroke upper extremity (UE) rehabilitation. However, the use of exergames without any follow-up by a health professional could lead to compensatory movements during the exercises, inadequate choice of difficulty level, exercises not being completed, and lack of motivation to pursue exercise programs, thereby decreasing their benefits. Combining telerehabilitation with exergames could allow continuous adjustment of the exercises and monitoring of the participant’s completion and adherence. At present, there is limited evidence regarding the feasibility or efficacy of combining telerehabilitation and exergames for stroke rehabilitation.

**Objective:**

This study aims to (1) determine the preliminary efficacy of using telerehabilitation combined with exergames on UE motor recovery, function, quality of life, and motivation in participants with chronic stroke, compared with conventional therapy (the graded repetitive arm supplementary program; GRASP); (2) examine the feasibility of using the technology with participants diagnosed with stroke at home; and (3) identify the obstacles and facilitators for its use by participants diagnosed with stroke and stroke therapists and understand the shared decision-making process.

**Methods:**

A mixed methods study protocol is proposed, including a randomized, blinded feasibility trial with an embedded multiple case study. The intervention consists of the provision of a remote rehabilitation program, during which participants will use the Jintronix exergame for UE training and the Reacts Application to conduct videoconferenced sessions with the therapists (physical or occupational therapists). We plan to recruit 52 participants diagnosed with stroke, randomly assigned to a control group (n=26; 2-month on-paper home exercise program: the GRASP with no supervision) and an experimental group (n=26; 2-month home program using the technology). The primary outcome is the Fugl-Meyer UE Assessment, a performance-based measure of UE impairment. The secondary outcomes are self-reported questionnaires and include the Motor Activity Log-28 (quality and frequency of use of the UE), Stroke Impact Scale-16 (the quality of life), and Treatment Self-Regulation Questionnaire (motivation). Feasibility data include process, resources, management, and scientific outcomes. Qualitative data will be collected by interviews with both participants and therapists.

**Results:**

At present, data collection was ongoing with one participant who had completed the exergame- telerehabilitation based intervention. We expect to collect preliminary efficacy data of this technology on the functional and motor recovery of the UE, following a stroke; collect feasibility data with users at home (adherence, safety, and technical difficulties); and identify the obstacles and facilitators for the technology use and understand the shared decision-making process.

**Conclusions:**

This paper describes the protocol underlying the study of a telerehabilitation-exergame technology to contribute to understanding its feasibility and preliminary efficacy for UE stroke rehabilitation.

**Trial Registration:**

ClinicalTrials.gov NCT03759106; http://clinicaltrials.gov/show/NCT03759106.

**International Registered Report Identifier (IRRID):**

DERR1-10.2196/14629

## Introduction

### Background

In up to 85% of stroke survivors, sequelae persist in the upper extremity (UE) [1], resulting in a long-term impact on daily living activities [2,3]. To stimulate neuroplastic changes that promote motor recovery, stroke survivors should follow an intensive, task-specific, stimulating, and, above all, repetitive exercise program [4]. However, the programs offered by conventional therapies, in particular, during chronic stage, are not sufficient for people to achieve the level of repetition and intensity required for recovery [4]. In Canada, patients diagnosed with stroke receive the Graded Repetitive Arm Supplementary Program (GRASP) [5] as a home exercise program after discharge from traditional rehabilitation services [3]. The GRASP is recommended by the Canadian Best Practice Recommendations for Stroke Care [3] to provide training and increase the use of the impaired arm in daily life activities [5]. However, patients must be motivated enough to do the exercises on their own and to perform enough repetitions to achieve improvement. A minimum of 15 hours is suggested for an intervention to result in a moderate improvement in daily living activities following a stroke [6]. Numerous studies offering an intensive exercise program, in chronic stroke, reported significant improvements in UE impairment (*P*=.05) [7,8] and even maintenance of these changes over a period of 6 months after treatment [8].

### Increasing Training Intensity in Stroke Rehabilitation

An interesting alternative that has been proposed to exercise intensity and exploit neuroplastic properties involves the use of virtual reality. For every 30 repetitions performed in a standard rehabilitation session, the same person can perform 600 to 800 repetitions within a 1-hour session in a virtual environment [4]. This is an important difference between the two approaches that highlights the potential of virtual reality. Thanks to its design, a virtual environment can simulate the real world while maintaining total control over the parameters of the tasks to be executed within it to foster motor learning [4]. In the context of rehabilitation, virtual reality has been integrated in the form of *exergames* because the gaming goal is to enhance activity through various types of exercises. Among these exergames, some have been specifically designed for stroke rehabilitation, including for balance training as well as for training for both lower and upper limb deficits (eg, Caren system, Lokomat, Armeo, and Jintronix [4,6,9,10]). The nature of the exergame interface makes it possible to modify the difficulty level of the exercises via various parameters such as intensity (time and repetition), visual feedback, speed, strength, and range of motion [4]. Progressing the exercise to ensure it remains challenging may motivate the user to complete the exercises [4]. However, there is no way to ensure that the movements made in the virtual environment are performed correspond to what is being trained. When performed in clinic, a health professional can ensure that the exercises are adjusted, and the movements are executed appropriately. However, at home, monitoring by a health professional needs to be considered to prevent compensatory movements during the exercises, inadequate choice of difficulty level, inappropriate completion of the exercises, and lack of motivation to pursue exercise program. The interfaces of the exergames do not allow automatic adjustment adapted to the person’s abilities and do not sufficiently detect compensations [4,6,9,10]. Thus, the follow-up by a therapist would make it possible to optimize the exergames’ benefits for the user (such as by adapting the difficulty parameters and by choosing games that are relevant for the user) and to help transfer motor learning from the virtual environment to activities of daily living.

To increase monitoring, a telerehabilitation system could allow such a follow-up through videoconferencing sessions between the user and the therapist. Such systems are increasingly used to provide remote rehabilitation services [11]. Its efficiency, compared with the standard treatment (face-to-face interventions), has been demonstrated, resulting in similar clinical results among participants diagnosed with stroke [12], therefore increasing accessibility to stroke rehabilitation services. Combining telerehabilitation with virtual reality (VirTele) could allow live sessions in which the therapist can observe the user playing and follow the game screen, at the same time, to assess how the user manages to complete the movements requested through the exercises (detect compensations, correct pathological patterns, and directly modify the difficulty setting necessary for the smooth running of the exercise). Therefore, the VirTele technology could allow continuous adjustment to the exercises and monitoring of the user completion to create a more personalized, tailored training program. Furthermore, in the long term, the VirTele exercise program could empower users to integrate the use of their impaired UE in their daily activities, through shared decisions made with the therapist.

### Study Objectives

Given the evidence for the efficacy of exergames as well as telerehabilitation for stroke rehabilitation, but the limited evidence of combining these technologies, such as in the VirTele program, the overall goals of this study are to explore its preliminary efficacy for UE rehabilitation and examine its feasibility for use with stroke survivors at home. More specifically, the objectives of this study are to (1) determine the preliminary efficacy of VirTele on UE motor recovery, function, quality of life, and motivation in participants with chronic stroke, compared with conventional therapy (GRASP); (2) examine the feasibility of using VirTele with participants diagnosed with chronic stroke at home; and (3) identify the obstacles and facilitators for the technology use by participants diagnosed with stroke and stroke therapists and understand the shared decision-making process.

It is hypothesized that the exergame-telerehabilitation program will lead to greater UE motor recovery than usual care (GRASP) in participants with chronic stroke. We also hypothesize that the exergame-telerehabilitation program will have a greater impact on function, quality of life, and motivation in participants with chronic stroke.

## Methods

### Study Design

This is a mixed method study design consisting of a randomized, blinded feasibility trial with an embedded multiple case study that will take place in Montreal, Canada. The randomized feasibility trial is a two-arm, single-blind trial design in which eligible participants will be randomly allocated to an experimental (VirTele for 8 weeks) or control, usual care group (GRASP for 8 weeks). The feasibility trial captures both feasibility and preliminary efficacy outcomes. Publishing the feasibility results would provide a better understanding of the context in which the efficacy data were collected and a better interpretation of the final results [13,14].

Outcome measures will be assessed for both groups on four occasions: at baseline (T1), at the end of 2-month intervention (T2), after a 1-month follow-up period (T3), and after a 2-month follow-up period (T4; Figure 1).

**Figure 1 figure1:**
[figure not shown]
Description of the outcome measurement time. GRASP: Graded Repetitive Arm Supplementary Program; VirTele: program that combines virtual reality exergame and telerehabilitation application.

Randomization and evaluations will be performed by research assistants who are not involved in the study. All participants will provide informed written consent before enrollment. This study is registered at clinicaltrials.gov (NCT03759106) and has received ethics approval from the Research Ethics Boards of Centre for Interdisciplinary Research in Rehabilitation of Greater Montreal (June 28, 2018).

### Participant Selection and Recruitment Strategy

At study entry, we will administer the Chedoke-McMaster arm component [15] to get evidence of UE impairment. Only participants with a score of 2 to 6 will be eligible. We will also verify balance maintenance during sitting position and detect any UE mobility restrictions limiting the ability to play (restricted shoulder movements because of pain) through active and passive mobilizations.

Stroke survivors who have residual UE deficits and are no longer receiving rehabilitation services will be eligible for study participation if they fulfill the eligibility criteria. The inclusion criteria are as follows: first-time unilateral ischemic or hemorrhagic stroke or no residual deficits from a previous stroke and able to use the Jintronix system (eg, able to move the game avatar with impaired limb). The exclusion criteria are as follows: being medically unstable (eg, uncontrolled cardiac condition), severe cognitive or communication deficits, visual impairments limiting the ability to use the games, and UE mobility restrictions limiting the ability to play (eg, restricted shoulder movements because of pain).

We intend to recruit participants from the community and from the archives of rehabilitation centers (offline) situated in the Montreal, Sherbrooke, and Laval areas (Quebec, Canada).

Study therapists (physical therapists or occupational therapists) from the different participating sites will also be included in the study to explore their experiences with the technology and comprehend the shared decision-making process underlying their choice of games and difficulty levels.

### Sampling

To date, no studies have reported on the use of combining such technologies, such as in the VirTele program so that this randomized, blinded feasibility trial will provide evidence for the effect size. However, as the first estimate of effect size, a sample size of 52 participants has been calculated using the Fugl-Meyer Upper Extremity Assessment as a primary outcome and G*Power 3.1 [16]. We assumed a medium effect size of 0.2, which was reported in a study with chronic stroke survivors with a 2-arm randomized clinical trial [17] and accounting for 20% retention issues (alpha=.05 and power=80%). This sample size corresponds to recommendations for pilot efficacy and feasibility trials [18] and is realistic, given time and budgetary constraints as well as recruitment potential. Thus, for the randomized, blinded feasibility trial, 52 participants will be recruited and randomly allocated to the experimental (n=26) or control group (n=26). A block randomization with a block size of six will be used, given time and material constraints.

For the multiple case study component, four therapists and the first 10 participants from the experimental group will be invited to participate in interviews. However, the final sample size of the participants diagnosed with stroke will be adjusted depending on the qualitative data saturation [19].

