### Data Analysis

#### Quantitative Data Analyses

Statistical analysis of the quantitative data will be performed using the Statistica software. Descriptive statistics will be used to report sociodemographic characteristics of participants (age, gender, handedness, and stroke characteristics) in both groups (experimental vs control). To address the first objective of the randomized, blinded feasibility trial, a mixed model approach will be applied for primary and secondary outcomes measure. Each model will contain one between-subject effect factor (group: control vs experimental), one within-subject effect factor (time: T1, T2, T3, and T4), and two covariates (gender and age) factors, which may impact exergame use. For each outcome measures, residual plots will be examined to verify normality and identify the best covariance structure. All the outcomes measure changes will be compared with the minimal clinically important differences. The effect size of the comparison between experimental and control groups will be calculated to estimate the final sample size. To address the second objective of the randomized, blinded feasibility trial, descriptive statistics (frequencies, means, and standard deviations) will be used to highlight the amount of exercise performed, the occurrence of adverse events, and participant and therapist satisfaction level in the experimental and control groups.

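### Arm severity (Chedoke-McMaster 2 to 6) is measured at entry but used neither to stratify the blocks of six nor to adjust the efficacy model, giving up balance and precision that would cost little to gain

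*Protocol article*

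**What the plan says.** Three places in the protocol article bear on this.

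- **Participant Selection and Recruitment Strategy.** "At study entry, we will administer the Chedoke-McMaster arm component [15] to get evidence of UE impairment", and "Only participants with a score of 2 to 6 will be eligible". Every eligible participant therefore has a severity score from 2 to 6 at entry.
- **Sampling.** "52 participants will be recruited and randomly allocated to the experimental (n=26) or control group (n=26"). The scheme is given in one sentence: "A block randomization with a block size of six will be used, given time and material constraints". No stratification factor appears here or elsewhere in the article.
- **Quantitative Data Analyses.** The mixed model has group, "one within-subject effect factor (time: T1, T2, T3, and T4"), and "two covariates (gender and age) factors, which may impact exergame use". The Chedoke-McMaster score is not in the model. The baseline Fugl-Meyer is there only as the T1 observation of the outcome. The same section says that the between-group effect size will be used to work out the final sample size.

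**The concern.** The primary outcome is a measure of upper-extremity impairment, and the entry range on a related scale is wide. How much a participant can gain, and how well they can carry out either program, plausibly depends on where they start. The article itself links both interventions to arm function: the control exercises are assigned by it, and game difficulty is tuned to motor skill. The two covariates that were chosen are justified by their bearing on exergame use, which concerns one arm only.

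The reason given for the blocking, time and material constraints, is a reason for keeping the arms level over calendar time. It is no reason to leave out a score that is already on file. At stake is the quality of the effect estimate: at 26 per arm, a chance difference in severity adds noise to a number that is to be carried into planning the larger trial.

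**Working it through.** **The plan's own figure.** The article gives no figure for balance. Its only related number is the total of 52, built on "We assumed a medium effect size of 0.2" and "accounting for 20% retention issues (alpha=.05 and power=80"%). The metric of the 0.2 is not stated. One reading comes close: a repeated-measures within-between interaction with f = 0.2, three occasions and correlation 0.5 needs 42, and 42 / (1 - 0.2) = 52.5, rounded up to 53. The point below uses only the 52 and the 26:26 split, not how they were reached.

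**Inputs.** N = 52, 26 per arm, blocks of six, scores 2 to 6 (all from the article). The distribution of scores is not given, so it is assumed and results are shown as ranges.

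**1. Imbalance in mean severity.** In SD units, the difference between arms in a baseline variable has standard error sqrt(2/26) = 0.277.

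- At least 0.3 SD: z = 0.3 / 0.277 = 1.08, two-sided probability 0.28.
- At least 0.5 SD: z = 0.5 / 0.277 = 1.80, two-sided probability 0.07.
- With about 21 completers per arm (26 less 20%), sqrt(2/21) = 0.309, and the probabilities become 0.33 and 0.11.

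A simulation of permuted blocks of six (20,000 runs for each of three assumed shapes over scores 2-6: uniform, peaked at 4, U-shaped) gives 27-29% and about 7%. Blocking over time does not change the picture.

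**2. Imbalance in the number of low scorers.** Let K of the 52 score 2-3, and let X of these fall in one arm. X is hypergeometric (52, K, 26), and the arms differ by |2X - K|.

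| K | Share of 52 | P(differ by 5 or more) |
|---|---|---|
| 16 | 31% | 0.132 |
| 17 | 33% | 0.237 |
| 18 | 35% | 0.144 |
| 19 | 37% | 0.249 |
| 20 | 38% | 0.153 |
| 21 | 40% | 0.258 |
| 22 | 42% | 0.160 |
| 23 | 44% | 0.264 |
| 24 | 46% | 0.164 |
| 25 | 48% | 0.267 |
| 26 | 50% | 0.165 |

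The range is 13-27%. The values alternate because the difference has the same parity as K, so for even K a difference of 5 or more means 6 or more.

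**3. What two strata would do.** With blocks of six inside strata 2-3 and 4-6, the difference within a stratum can never exceed 3. In the same simulation, an imbalance of at least 0.3 SD falls from 27-29% to 2-9%, and of at least 0.5 SD from about 7% to at most 0.4%.

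**4. What an imbalance does to the estimate (illustration).** Suppose the baseline outcome differs by 0.3 SD, SDs are equal over time, and the T1-T2 correlation r is 0.5 to 0.8 (all assumed).

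- An unadjusted T2 comparison shifts by 0.3 × r = 0.15 to 0.24 SD.
- A change-from-T1 contrast shifts by 0.3 × (1 - r) = 0.06 to 0.15 SD in the opposite direction.

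For the uneven split of low scorers, a difference of 5 is 5/26 = 0.19 of an arm. If mean gain differed by 0.5 SD between low and high scorers (assumed), the shift is 0.19 × 0.5 = about 0.10 SD, against a standard error of 0.28 SD.

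**The case against.** The strongest reply is that nothing here is wrong. Unstratified permuted blocks are valid, the usual type I error already allows for chance imbalance, and the article never promises balance on severity. That stands. A reader might infer that the comparison is biased; the documents do not support that.

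Second, a reader might infer that gender and age are the only baseline information used. They are not. T1 is a level of the time factor, so baseline Fugl-Meyer is in the model, and a group-by-time or change reading removes a difference in level. This stands in part. The analysis section does not name that interaction as the test, and T1 as an outcome does not deal with gain that depends on starting severity or with regression to the mean.

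Third, a reader might infer that severity imbalance is likely to create or mask a treatment effect. The illustrations do not show that: the shift from five extra low scorers is about 0.10 SD, well inside the standard error. The Discussion also already cautions against relying on feasibility results alone to establish efficacy.

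Fourth, quoting one case, such as 26% for 21 low scorers, would mislead, because one participant fewer gives 15%. Hence the range.

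Last, the number already randomised is not given, only that one participant had completed, so how much allocation could still be stratified is unknown. The full protocol is not shown and may say more about the allocation list. Both stand, and they are why the model comes first in the fix.

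**Conclusion.** The point holds as an optional but specific improvement. The article fixes a randomisation scheme and a covariate list that both leave out a severity score collected on everyone at entry. The cost is chance imbalance and lost precision, not invalidity: about a 28% chance of an imbalance of at least 0.3 SD and about 7% of at least 0.5 SD at 26 per arm, and 13-27% for a difference of five or more low scorers.

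The SD-based figures rest on a normal approximation confirmed by simulation under three assumed score distributions. The count-based range assumes that 31-50% score 2-3, and the cut at 2-3 versus 4-6 is illustrative. That severity predicts gain is plausible but is not quantified in the article. How much harm an imbalance would do depends on which contrast is tested, which the analysis section leaves open.

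**What to change.** **In the model (main change).** Add the Chedoke-McMaster arm score, or the baseline Fugl-Meyer, in one of two ways: with its interaction with time when T1 is kept as an outcome, or as a baseline covariate in a model of T2-T4 only. Baseline Fugl-Meyer fits the second form best, since in the first it is already the T1 outcome. A severity term that is constant over time is not enough: it moves T1 and later visits equally and so leaves a change-from-T1 contrast essentially untouched. Tabulate severity by arm. The cost is a few degrees of freedom and no new data.

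**In the randomisation, for participants not yet allocated.** Use permuted blocks of six within two severity strata, for example 2-3 and 4-6. Five strata would be too many for 52. This needs an amended allocation list. If the current block is completed before the switch, up to two blocks may be incomplete at the end instead of one. Even now 52 = 8 × 6 + 4, so exactly 26:26 is not guaranteed, and the arm totals and equipment demand may depart slightly further from it. If the list can no longer be changed, the model change alone recovers most of the benefit.
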